### Recruitment {15}

All women who have appointments at one of the six study centers during the recruitment period (November 2019–January 2021) and are potentially eligible for the study will be invited to participate. Study centers have a sufficient number of genetic tests every month to guarantee sufficient enrollment in the study.

## Assignment of interventions

### Sequence generation {16a}

The study IDs are assigned to the IG or CG by means of a randomized allocation sequence that was generated using computer-generated random numbers.

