### Trial design {8}

The trial is designed as a multicenter superiority parallel group trial with a 1:1 allocation ratio. Randomization will take place on an individual basis.

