### Study setting {9}

The study will be conducted in six centers for Familial Breast and Ovarian Cancer in Germany (Cologne, Heidelberg, Kiel, Würzburg, Munich, and Dresden) which belong to the German Consortium for Familial Breast and Ovarian Cancer and are part of university hospitals. These clinics were chosen because they are the largest centers in terms of numbers of cases and performed genetic testing and they are spread throughout Germany.

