##### Optimized standard care

The centers of the German Consortium for Familial Breast and Ovarian Cancer already have, to varying degrees, an advisory infrastructure with training in risk communication and general communication techniques for the physicians in charge of counseling. In order to ensure the comparability of all centers, all physicians who supervise women participating in the study must have participated in 2.5-day communication skills training with a refresher session using actor patients, own difficult cases, role plays, and video tapes based on KoMPASS training [38]. The participating physicians will be trained in communication techniques such as the basics of counseling techniques, breaking bad news, dealing with difficult emotions, dealing with death and dying, using teach-back, and learning to communicate complex medical content in a comprehensible way. Physicians own challenging sample cases are used as a central basis for effective, learner-centered training (“experiential training”). The evaluation of these simulations takes place through the analysis of video recordings of the interactions.

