### Participant timeline {13}

Women who are potentially eligible for the study but have not yet been tested for a *BRCA1/2* gene mutation will be informed about the study at their appointment for collecting the blood sample for genetic testing. Approximately 4 weeks after collection of the blood sample, the women have an appointment to discuss the test results with their physicians. During this appointment, only women with a positive *BRCA1/2* test result will be invited to participate in the study, and their informed consent will be obtained. Women who have previously been tested positive for *BRCA1/2* at a different facility from the six study centers will be invited to participate during their first consultation at the respective study center. Women who are *BRCA1/2* mutation carriers and have already joined the intensified breast-cancer screening program will be invited to participate during their semi-annual appointment. Physicians will complete a recruitment form in which they can also document reasons for non-participation.

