### Implementation {16c}

At baseline, each woman is assigned a study ID by means of prenumbered envelopes. Only after the women have sent back the baseline questionnaire to the research team will the respective clinic in which the women were recruited will be informed which group the study ID was assigned to via an encrypted e-mail by the research team. The six study centers have no means of accessing the group allocations before baseline measures are obtained.

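### The stated primary t-test contains group only; adding center and recruitment route as pre-specified factors would cost little and gain a little precision

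*Protocol article*

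**What the plan says.** Trial design {8} describes a "multicenter superiority parallel group trial with a 1:1 allocation ratio" and adds: "Randomization will take place on an individual basis". Sequence generation {16a} speaks of a "randomized allocation sequence that was generated using computer-generated random numbers". Neither that item nor those on trial design, baseline data and allocation, concealment and implementation mention blocks, strata or minimization, and none of them rules these out.

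On the setting: "The study will be conducted in six centers for Familial Breast and Ovarian Cancer in Germany". The section on optimized standard care says these centers "already have, to varying degrees, an advisory infrastructure with training in risk communication and general communication techniques". It then requires the same 2.5-day communication training of all physicians supervising participants, to make the centers comparable.

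Participant timeline {13} gives three routes into the trial: women who receive a new positive result at a study center, carriers tested elsewhere who come for a first consultation, and carriers who "have already joined the intensified breast-cancer screening program will be invited to participate during their semi-annual appointment".

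Statistical methods {20a} fixes the primary analysis as a one-sided t-test between the two groups on the congruence between the role preferred at baseline and the role actually played at t1. A later sentence, placed after the secondary outcomes, adds demographic data as explanatory variables. It names neither center nor route.

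**The concern.** The primary outcome compares the role a woman wanted with the role she played. How counseling is delivered at her center could affect this. So could whether she has just learned her result or has already taken up one of the options that the decision aid covers. If so, part of the outcome variance is explained by two facts that are known at enrollment, and the stated test leaves that part in the error term.

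This does not depend on how the list was made. With a simple list, chance differences between the arms in center and route mix stay in the estimate. With a stratified list, the arms are balanced but the plain t-test still computes its standard error as if they were not. At stake are some precision and an avoidable argument afterwards if one arm happens to hold more women already in screening.

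**Working it through.** **Inputs.** From Sample size {14}: d = 0.3, power 0.80, alpha 0.05, drop-out 30%, 199 per group. From Statistical methods {20a}: one-sided t-test. R², the share of outcome variance explained by center and route, is not in the documents; 2%, 5% and 10% are assumed.

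**Reproducing the planned size.** By the noncentral t distribution, the one-sided test needs 139 per group; 139 / 0.7 = 198.6, so 199 per group and 398 in total. The two-sided test named in the sample size section would need 176 per group; 176 / 0.7 = 251.4, so 252 per group and 504 in total. The planned 398 therefore matches the one-sided test of the analysis section. The disagreement between the two sections is a separate matter. The base used here is 139 evaluable per arm (N = 278), one-sided 0.05, where the unadjusted test has 80.2% power.

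**Chance shift under a simple list.** The 95% range of the shift in the arm difference due to center and route is ±1.96 × √(R² × 4/278), in SD units:
- R² = 0.02: ±0.03
- R² = 0.05: ±0.05
- R² = 0.10: ±0.07

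The unadjusted 95% half-width is 1.96 × √(4/278) = 0.235 SD. The shift is part of that half-width and does not come on top of it. Removing it entirely reduces 0.235 to 0.235 × √(1 − R²): 0.229 at R² = 0.05 and 0.223 at R² = 0.10. In simulation (5,000 runs, simple list, plain t-test) the mean estimate was 0.30 and the type I error 0.050.

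**Type I error under a stratified list with the plain t-test.** The true standard error is smaller than the computed one by √(1 − R²), so the effective critical value is 1.645 / √(1 − R²). At R² = 0.10 this is 1.734, a one-sided error of 0.041. Simulated values were 0.048, 0.046 and 0.041 for R² = 0.02, 0.05 and 0.10.

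**Power with adjustment.** The proposed model adds k = 6 terms (five for center, one for route). Under a simple list, estimating them inflates the variance by about 1 + k/(N − k − 3) = 1 + 6/269 = 1.022. The effective effect size is then 0.3 / √((1 − R²) × 1.022), tested on 278 − 8 = 270 degrees of freedom. With balanced strata the inflation is about 1.

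| R² | Unadjusted, simple list | Adjusted, simple list | Adjusted, balanced strata (upper bound) |
|---|---|---|---|
| 0.02 | 80.2% | 80.2% | 80.9% |
| 0.05 | 80.2% | 81.2% | 82.0% |
| 0.10 | 80.2% | 83.0% | 83.8% |

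Simulation with 18 center-by-route cells and blocks of four gave 80.5%, 81.5% and 83.1% for stratifying plus adjusting. Stratifying while keeping the plain t-test gave 80.3%, 80.6% and 81.2% (simulation error about 0.6 points). Most of the gain therefore comes from the model and not from the list.

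One caution follows from the same simulation. Fitting all 18 cells under a simple list gave 78.8%, 79.9% and 81.9%, against about 80.4% unadjusted. At small R² an overfilled model costs power, so main effects only should be used.

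**The case against.** The strongest case against is that little is at stake. The unadjusted comparison is valid, simple randomization of 398 women is defensible, and the document gives no evidence that center or route predicts role congruence. The common physician training is meant to reduce differences between centers. Covariates are often left to a statistical analysis plan, which is not shown. All of this stands as to size. It does not remove the point, because the article does not leave the primary model open: it states a t-test on group alone.

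Three stronger readings are tempting and are not supported.
- A reader might infer that the trial uses a single unrestricted sequence. The text neither says so nor excludes restriction, and a condensed article may omit it.
- A reader might call center and route known prognostic factors. No section says this; plausibly prognostic is as far as the text allows.
- A reader might infer that, because "each woman is assigned a study ID by means of prenumbered envelopes" at baseline, numbers used by women who never return the questionnaire upset the balance. Under a simple list there is no engineered balance to upset, and losses before the arm is disclosed are unrelated to arm.

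Nor does it follow that the list should be replaced. Recruitment began in November 2019. A new stratified list would disturb a running envelope system, leave incomplete blocks in many small strata and add some predictability in an open-label trial. Without adjustment in the analysis it would gain about one point of power or less.

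**Conclusion.** The point holds as a low-cost improvement to the stated primary analysis and not as an error in the randomization. The planned test ignores two plausibly prognostic factors that are known or easily recorded. The consequence is precision only: a small loss under a simple list, and a slightly conservative test (type I error 0.048 to 0.041) under a stratified one. Adjustment is worth about 0 to 3 points of power at 139 evaluable women per arm, one-sided 0.05. That range rests on the assumed R² of 2% to 10% and on 30% drop-out. If R² is below about 2%, adjusting under a simple list gains nothing in power; its remaining use is that the choice is made before results are seen.

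**What to change.** In Statistical methods {20a}, replace the unadjusted t-test by a linear model for the primary outcome with group, center (six levels) and recruitment route (new result versus known carrier) as pre-specified fixed main effects, without interactions. The group coefficient and its confidence interval become the primary result; the plain t-test can be kept as a sensitivity analysis. Make the change before any outcome data are compared by arm.

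Record route for every woman on the recruitment form that physicians already complete, and complete it for women already enrolled. Center is known, since the research team reports each allocation to the recruiting clinic. Blinding {17a} removes study IDs from the data set before analysis, so center and route must be kept there as coded variables.

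Add one sentence to Sequence generation {16a} saying whether the list was blocked or stratified. Block sizes can be withheld. If there were strata, they belong in the model.

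Cost: a short amendment, one field on a form and six degrees of freedom (276 to 270). No additional participants and no new allocation list are needed.

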### Allocation concealment mechanism {16b}

Only the members of the research team at the data evaluation institute know the allocation of the study IDs to the groups. The list with study IDs and group allocations is password protected and only accessible by the research team.

### Implementation {16c}

At baseline, each woman is assigned a study ID by means of prenumbered envelopes. Only after the women have sent back the baseline questionnaire to the research team will the respective clinic in which the women were recruited will be informed which group the study ID was assigned to via an encrypted e-mail by the research team. The six study centers have no means of accessing the group allocations before baseline measures are obtained.

### Blinding {17a}

Due to the nature of the study, study participants and the treating physicians cannot be blinded. The members of the research team responsible for analyzing the data will be blinded to group allocation by removing study IDs of the data set prior to data analysis.

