### Objectives {7}

The EDCP-BRCA study aims to assess the effectiveness of decision coaching combined with a decision aid. The main hypothesis is that *BRCA1/2* mutation carriers who receive nurse-led decision coaching and a decision aid will show a higher congruence between the role they preferred to play in the decision-making process and the role they actually played. Secondly, we hypothesize that women who receive nurse-led decision coaching combined with a decision aid show higher satisfaction with the role they played in the decision-making process when compared to the control group. Additional objectives of the study are to evaluate whether decisional conflict and psychological burdens can be decreased and knowledge about the different preventive options can be increased.

Additionally, process evaluation will be conducted alongside the study to identify the barriers and facilitating factors of implementation. Secondly, the nurses and participating women are asked to share their experiences of the intervention. Finally, the process evaluation aims at investigating the underlying mechanisms of the intervention in relation to the context and interpreting summative results considering the impact of the intervention.

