### Unblinding {17b}

The design is open label with only data analysts being blinded so unblinding will not occur.

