## Statistical methods

### Statistical methods {20a}

Baseline data will be analyzed to guarantee comparability of both groups. Mean differences of the primary outcome in both groups (congruence between preferred role at baseline and actual role in the decision-making process at t1) will be compared using an independent samples one-sided *t*-test with the group allocation as the independent variable. All secondary outcomes will be analyzed via independent samples *t*-tests, Chi-square tests, or nonparametric tests in case of non-normality. Beyond group allocation, demographic data will be used as the independent variable. All data analysis will be performed with SPSS and R.

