### Protocol non-adherence and missing data {20c}

Data analysis will be conducted according to the intention-to-treat method. Imputation of missing data is not planned. Additionally, a per-protocol analysis is planned as a sensitivity analysis to exclude participants who did not comply with the allocated intervention by missing the decision coaching or by failing to return all questionnaires.

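### Removing study IDs does not mask the arm variable, so the stated method does not secure the analyst blinding that the protocol claims

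*Protocol article*

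**What the plan says.** All references are to the protocol article.

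- **Blinding {17a}:** participants and treating physicians cannot be blinded. The research team members who analyse the data "will be blinded to group allocation by removing study IDs of the data set prior to data analysis". No other masking step is described.
- **Unblinding {17b}:** "The design is open label with only data analysts being blinded so unblinding will not occur".
- **Allocation concealment mechanism {16b}:** on who holds the allocations, this section says: "Only the members of the research team at the data evaluation institute know the allocation of the study IDs to the groups". Access to the password-protected list lies with the research team.
- **Statistical methods {20a}:** the primary outcome is compared by an "independent samples one-sided" t-test "with the group allocation as the independent variable".
- **Objectives {7}:** the direction is fixed. Women who receive the intervention "will show a higher congruence between the role they preferred to play in the decision-making process and the role they actually played".
- **Protocol non-adherence and missing data {20c}:** the main analysis is by intention to treat. A per-protocol sensitivity analysis leaves out women who did not comply "by missing the decision coaching or by failing to return all questionnaires".
- **Explanation for choice of comparators {6b}:** control women are not offered coaching.

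**The concern.** Blinding {17a} states both the aim and the method by which it is reached, and the method does not match the aim. An ID is a key to the list, whereas the arm is a separate column. If the arm column carries its real labels, an analyst who never sees an ID still knows who is in which group.

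This deserves attention because nothing else in the trial is masked. Women and physicians know the allocation, the nurses deliver the coaching, and the outcomes are questionnaire self-reports. A reader of the results paper will take the claim of blinded analysts at face value.

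Some decisions that blinding would cover are also open in this text. The congruence score is described only as the difference between desired and actual role, without saying whether it is signed or absolute. Tests for secondary outcomes depend on whether the data look normal. An analysis plan may settle these, so they are not faulted here. They only show what blinding would be for.

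**Working it through.** The plan gives no figure on this point, so the check sets its statements side by side.

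**Step 1. What ID removal achieves.** The list links each study ID to an arm (Allocation concealment {16b}). Without IDs, an analyst cannot look up a record in that list. This is a real but partial protection.

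**Step 2. What it leaves in place.** The primary test uses group allocation as the independent variable (Statistical methods {20a}), so the arm must be in the analysed data set. The article mentions no neutral code for it, no holder of such a code and no time at which a code is broken. ID removal therefore leaves the arm as visible as it was before.

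**Step 3. Who can see the list.** The research team at the data evaluation institute knows the allocations and has access to the list {16b}. The research team also e-mails each allocation to the clinic (Implementation {16c}). The analysts are members of the research team {17a}. The article does not say that those who analyse are kept from the list.

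**Step 4. Whether a code would survive the per-protocol rule.** Suppose that the arms were coded A and B. The possible reasons for exclusion under {20c} are:

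| Reason for exclusion | Possible in intervention group | Possible in control group |
|---|---|---|
| Missed coaching | yes | no, coaching is not offered {6b} |
| Not all questionnaires returned | yes | yes |

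Whether the questionnaires were returned can be seen in the data. A woman with every questionnaire returned who is nevertheless excluded can only have missed coaching, so she is in the intervention group. One such record shows which code is the intervention group, even if both reasons are merged into a single flag. The coded analysis stays masked only if the analysts receive these exclusions after it is complete.

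**Step 5. Whether the statement on unblinding fits.** Unblinding {17b} says that unblinding will not occur. If the arm is not coded, there is no analyst blinding to break. If it is coded, someone must learn which code is the intervention group before a directional result can be read. Either way, the plan needs a stated point of code break.

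**The case against.** The strongest reply is that the article is a condensed protocol. It states the aim of blinded analysts and one relevant step. A neutral code is neither described nor excluded, and such detail is often left to the full protocol or analysis plan. The analysts are a subset of the team, so overlap with the list holders is not shown. This stands in part: the documents do not show that the analysts will in fact be unblinded. It does not rescue the stated method, because the article says how blinding is reached and that step alone does not reach it.

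Three stronger readings are tempting and are not supported.

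- **A reader might infer that the one-sided test by itself unblinds the analyst.** It does not. The t statistic can be computed on A/B codes, and the direction applied once the code is opened.
- **A reader might infer that the per-protocol analysis makes blinding impossible.** It is a sensitivity analysis, and nothing prevents it from being run last or its exclusions from being applied by someone else.
- **A reader might infer an inflated false-positive rate for the primary outcome.** The choice of nonparametric tests is stated for secondary outcomes; the primary test is fixed as a t-test. Picking the most extreme of several tests also raises the error rate when the arms are coded, so such inflation measures choice among tests and not knowledge of the arm.

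It is also true that analyst blinding cannot reduce reporting bias from unblinded women.

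**Conclusion.** The point holds in a limited form. Removing study IDs does not mask the arm variable, no separation between list access and analysis is stated, and the missed-coaching exclusion would reveal a coded arm unless it comes last. The only masking that the trial claims is therefore not secured by the stated method. To say that blinding will fail in practice would go too far, because a code may be specified in a document not shown.

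The weight is low. The primary test and its direction are prespecified, so little room is left for knowledge of the arm to act on the primary result, and the expected effect there is small. The scoring of congruence and the choice of secondary tests are somewhat more exposed if no analysis plan fixes them. No number is attached, because the documents give no basis for one.

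The conclusion assumes that the analysed data set carries the arm with its real labels, or under a code that the analysts could resolve. The article neither confirms nor rules this out.

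**What to change.** 1. In Blinding {17a}, replace ID removal as the sole step. The analysts receive a data set with a random A/B arm code, made and held by a list-holding team member who does not analyse.
2. In Allocation concealment {16b}, state that those who analyse have no access to the allocation list.
3. Fix the congruence scoring and the choice of tests for secondary outcomes on the coded data, then run the intention-to-treat analysis on the same coded data.
4. Break the code to apply the direction of the primary hypothesis. Release the per-protocol exclusions to the analysts only after that, and run that analysis last.
5. In Unblinding {17b}, state when the code is broken and by whom.

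If the team does not want these steps, it should withdraw the claim that the analysts are blinded and describe the analysis as open.

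The cost is one recoding step, short edits to three sections, and strict separation of list holder and analyst within the existing team. The article names no such separate person, so the team must designate one. Sample size, data collection and the primary test are unaffected.
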